#### Primary Analysis

The study will yield information about safety, tolerability, and efficacy. The main focus of the primary analysis is to determine whether either one or both doses are safe and tolerable. Each patient will be treated with fasudil or placebo over 45 min twice a day for 20 days. Significant drug intolerance will result in stopping the infusion and termination of the trial participation for this patient.

The proportions of patients for whom the treatment is tolerable/safe are derived for each treatment group. For both active treatment groups and for both, safety and tolerability, separately the difference in proportions to the placebo group will be calculated with its 95% confidence interval. Subsequent analyses will model tolerability and safety in logistic regressions adjusting for randomization stratification factors and important prognostic factors assessed at baseline. Treatment group differences will be reported in terms of odds ratios with 95% confidence intervals.

Primary analyses of safety and tolerability will be carried out on the ITT population. For the purpose of the tolerability analyses, subjects who discontinue during the treatment period will be considered as worst case, i.e., no drug tolerability. If a number of patients withdraw from the study following completion of the treatment period, there observations will be dealt with as independent right censoring and the time to first drug-related SAE will be considered as primary endpoint. The difference in proportions free of any drug-related SAE at V23 will be assessed using Kaplan-Meier estimates and corresponding 95% confidence intervals. Subsequent analyses will model time to first drug-related SAE in Cox proportional hazard regressions adjusting for randomization stratification factors and important prognostic factors assessed at baseline. Treatment group differences will be reported in terms of hazard ratios with 95% confidence intervals. The ITT analyses will be complemented with a per-protocol (PP) analysis. Differences between both analyses will be reported and evaluated in detail.

#### Secondary Analysis

##### Efficacy

Efficacy outcomes including ALSFRS-R, ALSAQ-5, SVC, and MUNIX through to visit V23 will be analyzed by means of Gaussian linear model for repeated measures (so-called MMRM) with treatment group, time (visits V20, V22, V23), treatment-by-time interaction, region, and stratum of onset as factors and baseline measurements of the outcome as covariate. The error terms are assumed to follow a multivariate normal distribution with unstructured covariance. Least squares mean changes from baseline will be reported for the treatment groups with 95% confidence interval (CI) as well as the difference between the least squares treatment group means with 95% CI and *p*-value testing the null hypothesis of no treatment effect. The analysis will be primarily performed on the ITT population, but complemented by PP analysis.

Survival time will be used as a secondary endpoint. The Kaplan-Meier method will be applied to estimate the survival probabilities in each group. The 95% CIs will be calculated with the variance derived according to Greenwoods' formula. Subjects will be right-censored at end of their follow-up. Pairwise group comparisons against placebo will be analyzed using exact log rank tests. Cox proportional hazards regression will be carried out if there are a sufficient number of events.

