•Probable (clinically or laboratory) or definite ALS according to the revised version of the El Escorial World Federation of Neurology criteria •Disease duration more than 6 months and less than 18 months (inclusive). Disease onset defined as date of first muscle weakness, excluding fasciculations and cramps •Vital capacity more than 65% of normal (SVC; best of three measurements) •Age: ≥18 years •Patients have to be treated with Riluzole (2 × 50 mg/d), must be stable for at least 4 weeks before randomization •Patients who have started on Edaravone therapy shall continue Edaravone treatment. Edaravone treatment must not be discontinued for reasons of trial participation. •Women of childbearing age must be non-lactating and surgically sterile or using a highly effective method of birth control and have a negative pregnancy test. Acceptable methods of birth control with a low failure rate i.e., <1% per year) when used consistently and correct are such as implants, injectables, combined oral contraceptives, hormonal intrauterine devices (IUDs), sexual abstinence or vasectomized partner •Capable of thoroughly understanding all information given and giving full informed consent according to GCP •Patients have to have a valid health insurance, when recruited in a center in France	•Previous participation in another clinical study involving trial medication within the preceding 12 weeks or five terminal half times of the longest to be eliminated trial medications (whichever is longer) or previous participation in this trial •Tracheostomy or continuous assisted ventilation of any type during the preceding 3 months before randomization or a significant pulmonary disorder not attributed to ALS, which may complicate the evaluation of respiratory function, intermittent non-invasive ventilation is permitted. •Patients with a history of intracranial bleeding, known intracerebral aneurysms or Moyamoya disease, or positive family history for the above. If only family history positive, MR- or X-ray-based cranial imaging not older than 24 months must confirm absence of bleeding, aneurysms or Moyamoya. •Gastrostomy •Any medical condition known to have an association with motor neuron dysfunction or involving neuromuscular weakness or another neurodegenerative disease, e.g., PD or AD, which might confound or obscure the diagnosis of ALS •Presence of any concomitant life-threatening disease or impairment likely to interfere with functional assessment •Patients with known arterial hypotension (resting blood pressure <90/60 mmHg) or previous hypotensive episodes or requiring treatment for increasing of blood pressure, such as fludrocortisone, midodrine, etilefrine, cafedrine, or theodrenaline •Patients with an uncontrollable or unstable arterial hypertensive disease (resting blood pressure >180 mmHg systolic and/or >120 mmHg diastolic under current antihypertensive medication) •Known pulmonary hypertension and any medication prescribed for treatment of pulmonary hypertension •Confirmed hepatic insufficiency or abnormal liver function (stable ASAT and/or ALAT >3 times the upper limit of the normal range) and determined to be non-transient through repeat testing •Renal insufficiency with a glomerular filtration rate (GFR) <60 ml/min/1.73 m^2^ (calculated by MDRD equation) and determined to be non-transient through repeat testing •Major psychiatric disorder, significant cognitive impairment or clinically evident dementia precluding evaluation of symptoms •Hypersensitivity to any component of the study drug •Liable to be not cooperative or comply with the trial requirements (as assessed by the investigator), or unable to be reached in the case of emergency •Pregnant or breast-feeding females or females with childbearing potential, if no adequate contraceptive measures are used •Prisoners or subjects who are involuntary incarcerated •Patients subject to legal protection measures

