### Randomization, Stratification and Blinding

This trial has three parallel groups: fasudil 15 mg twice daily, fasudil 30 mg twice daily, and matching placebo. Patients are randomized to treatment using an allocation ratio of 1:1:1. The randomization list will be centrally generated using a computerized system stratified by geographical region and type of onset (bulbar, spinal). Patients will be assigned to the bulbar or spinal stratum according to the location of the earliest experienced ALS symptom (defined by the first muscle weakness or in the case of bulbar onset, by the presence of dysarthria and/or dysphagia). In the case of a patient with simultaneous onset of spinal and bulbar symptoms, onset will be defined as bulbar. Cervical and respiratory onsets are stratified to the spinal onset stratum. The randomization list will be generated by the Biometry and Bioinformatics Core using a pseudo-random number generator.

This study includes double-blind (participant- and investigator blind) treatment. Study medication will be packed and blinded by the Pharmacy at University of Leipzig Medical Center, Germany, according to the randomization list. Each patient medication package will be sent together with the sealed unblinding codes to the sites. The investigator at the site will take care that each patient is provided with the study medication box of the correct randomization number. The randomization list will be kept in safe and confidential custody at Pharmacy at University of Leipzig Medical Center, Germany. For all patients, emergency codes will be available to the investigator. A code, which reveals the treatment group for a specific study patient, may be opened during the study only if the choice of treatment depends on the study subject's therapy assignment. During the study, emergency unblinding should occur only by accessing the study patient's emergency code.

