### Statistical Analysis

#### Sample Size Calculation

A sample size of 102 patients (i.e., 34 patients per treatment group) yields sufficiently narrow confidence intervals for the difference in proportions between the placebo group and the treatment groups for both primary endpoints, the proportion of patients without drug-related SAEs and the proportion of patients without treatment intolerability. Under the assumption of no difference between the treatment groups and the placebo group the half-width of the 95% confidence interval for the difference in proportions is at most 0.24. Expected are high proportions of tolerability and safety in which case the confidence interval becomes narrower. If the proportion is for instance 0.9 the half-width reduces to 0.14, which is considered sufficiently narrow. Calculations were carried out using the software nQuery 4.0. Adjusting for dropout of 15% we aim to recruit a total number of 120 patients (i.e., 40 patients per treatment group).

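### The efficacy MMRM fits one baseline slope to all three visits; a baseline-by-visit term would modestly sharpen the day-180 comparison

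*Protocol article*

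**What the plan says.** The Efficacy text under Secondary Analysis lists the MMRM terms: treatment, visit (V20, V22, V23), their interaction, and then "region, and stratum of onset as factors and baseline measurements of the outcome as covariate", with an unstructured covariance. Table 2 puts these visits at days 26, 90 and 180. The treatment effect and the covariance may differ between visits, but the baseline coefficient may not.

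For survival the same section says "Pairwise group comparisons against placebo will be analyzed using exact log rank tests" and mentions no strata. Cox regression follows only if there are enough events, and its covariates are left open. Randomisation is "stratified by geographical region and type of onset (bulbar, spinal" (Randomization, Stratification and Blinding). Both randomisation factors are therefore in the MMRM, and neither appears in the log-rank test as described.

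The sample size rests on confidence-interval width for safety and tolerability. Efficacy is secondary, and the Discussion accepts that the trial may be too small to show a significant improvement.

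**The concern.** Patients enter 6 to 18 months after onset (Table 1), so a baseline ALSFRS-R score partly reflects how fast the patient has already declined. If past speed predicts future speed, the relation between baseline and change is weak at day 26, when little decline has accrued, and stronger at day 180. Residual variance is smallest at day 26, so under an unstructured covariance the common slope is weighted towards that visit. The day-180 comparison, where a lasting effect would be looked for, then gets too little adjustment.

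At stake is the width of the interval for that difference, and how much of a chance baseline imbalance stays in the estimate. The log-rank test raises a smaller issue of the same kind: patients are randomised within onset type, but the test as described does not use it.

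**Working it through.** **1. The plan's own figures.** The Sample Size Calculation has 34 evaluable patients per arm. The half-width is 1.96 × √(2p(1−p)/34).
- p = 0.5: 1.96 × √(0.5/34) = 0.238. The plan says "the half-width of the 95% confidence interval for the difference in proportions is at most 0.24".
- p = 0.9: 1.96 × √(0.18/34) = 0.143. The plan says "If the proportion is for instance 0.9 the half-width reduces to 0.14".
- Dropout: 102/(1 − 0.15) = 120.

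All three reproduce. No efficacy precision or power is stated, so there is no efficacy figure to correct.

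**2. How the common slope acts.** Take complete data and set region and onset aside. Because treatment-by-visit is saturated, the day-180 contrast is the difference in mean change minus b × the difference in baseline means.
- With its own slope b₁₈₀, the variance is proportional to σ², the residual variance at day 180.
- With a common slope b, it is proportional to σ² + (b₁₈₀ − b)² × Var(baseline).

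The ratio of the first to the second is 1 − r². Here r is the within-arm correlation of baseline with the day-180 residual that the common slope leaves. For r = 0.1, 0.2, 0.3, 0.4, 0.5 the ratio is 0.99, 0.96, 0.91, 0.84, 0.75. Estimating one more slope costs about 1% at 34 per arm.

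**3. Simulated size for ALSFRS-R.** The documents do not give r, so it must come from assumptions. Runs A and B assume future slopes with mean 0.9 and SD 0.6 points per month, measurement SD 1.5 and complete data. Run A also takes duration as uniform over 6–18 months and a scale maximum of 48. Run C is a further run under assumed slopes. Run A has 120 patients and 500 trials per setting; Run B has 102 and 600; Run C has 102.

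Entries are the day-180 variance relative to the stated model. The first figure is baseline-by-visit alone; the second adds log progression rate by visit.

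| Past/future slope correlation | Run A | Run B | Run C |
|---|---|---|---|
| 0 | 1.01 / 1.01 | – | 1.01 / 1.02 |
| 0.2 | 0.99 / 0.99 | – | – |
| 0.3 | – | 0.99 / 1.01 | 0.95 / 0.97 |
| 0.4 | 0.94 / 0.95 | – | – |
| 0.5 | – | 0.91 / 0.92 | 0.94 / 0.95 |
| 0.6 | 0.90 / 0.91 | – | – |
| 0.7 | – | 0.85 / 0.85 | 0.82 / 0.81 |
| 0.8 | 0.80 / 0.79 | – | – |

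Runs at the same correlation differ by up to 0.04, so the second decimal should not be over-read.

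**4. What this buys.**
- Ratio 0.94: interval width × √0.94 = 0.97, equivalent to 34/0.94 ≈ 36 per arm (r = √0.06 ≈ 0.24).
- Ratio 0.80: interval width × √0.80 = 0.89, equivalent to 34/0.80 = 42.5 per arm (r = √0.20 ≈ 0.45).

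**5. Progression rate.** In the table it moves the ratio by at most 0.02 in either direction once baseline-by-visit is present. As a main effect only, Run A gives 0.99, 1.00, 1.01, 1.03, 1.03 at correlations 0, 0.2, 0.4, 0.6, 0.8, which is no gain.

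**6. Log-rank test.** Simulated 40 v 40 over six months with 30% bulbar onset, using the asymptotic test in place of the exact one. Power is unstratified v onset-stratified.
- Treatment HR 0.5, bulbar HR 2, with 5, 10 and 20% placebo deaths in the spinal stratum: 8.4 v 8.3%, 14.8 v 14.9%, 25.0 v 25.6%.
- Largest gain (treatment HR 0.3, bulbar HR 3, 20% deaths): 58.3 v 61.1%.
- Largest loss (treatment HR 0.3, bulbar HR 1, 10% deaths): 23.0 v 22.6%.
- With no treatment effect, the unstratified test rejected in 4.4 to 5.4% of trials.

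**The case against.** The strongest reply is that this is a preference and not an error. The MMRM already adjusts for the outcome's baseline and both randomisation factors. Efficacy is secondary with no power claimed, and the full protocol or SAP may add terms that a journal article leaves out. Most of this stands. What remains is that the article gives an explicit list of terms with visit crossed only with treatment, and an SAP that follows that list inherits the single slope.

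Four stronger readings are tempting and are not supported:

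- **That the missing pre-trial progression rate is the main loss.** The data exist: V1 ALSFRS-R is collected, and Table 1 has "Disease onset defined as date of first muscle weakness, excluding fasciculations and cramps". A further simulation with both terms together (120 patients, 1,500 trials per setting) gives variance ratios of (0.927/0.937)² = 0.98, (0.847/0.901)² = 0.88 and (0.800/0.899)² = 0.79 at correlations 0.3, 0.5 and 0.7. It cannot say which term earned the gain; step 5 shows that it is baseline-by-visit. The log of the rate is also undefined for a patient scoring 48, and Table 1 sets no ALSFRS-R ceiling.
- **That the gain comes free.** It depends on a correlation the documents do not give, and it is slightly negative if that correlation is zero.
- **That the plan adjusts its primary models for prognosis but not its efficacy model.** Under Primary Analysis the main comparison is an unadjusted difference in proportions or Kaplan-Meier estimates. The adjusted logistic and Cox models come afterwards.
- **That go/no-go for phase IIb rests on the efficacy estimate.** The Discussion makes the next study conditional on tolerance and safety, and says that non-significant efficacy alone would not stop it.

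**Conclusion.** This is a minor gain in efficiency on a secondary endpoint. The planned analysis is valid, and no stated figure or decision rule changes.

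For ALSFRS-R, baseline-by-visit should reduce the day-180 variance by about 0 to 6% at low past/future slope correlation and by about 6 to 20% at moderate to high correlation. The downside is about 1%. These figures rest on the assumed slopes, measurement error and complete data above. Nothing was simulated for SVC, MUNIX or ALSAQ-5, where the argument is only by analogy.

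A reader might infer that the unstratified log-rank test is faulty or costs real power. The simulations do not show that: power changes by 0 to about 3 points, and by under 1 point where deaths are 10% or fewer and the bulbar HR is 2 or less. The reason to stratify is consistency with the randomisation.

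**What to change.** Before unblinding, pre-specify the following:

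1. Add a baseline-by-visit interaction to the MMRM for ALSFRS-R, ALSAQ-5, SVC and MUNIX. Three baseline slopes replace one, so the cost is two degrees of freedom and no new data.
2. State that the exact log-rank test is stratified by onset type. Add region only if there are enough deaths to avoid near-empty strata.
3. Treat pre-trial progression rate as optional at most. If used, cross it with visit and give a rule for a baseline score of 48.

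This is a change of wording in the analysis plan. If the full SAP already contains the first two items, nothing further is needed.

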### Study Procedures

The trial is structured into 24 visits (V0–V23). V0 is the screening visit and may take place up to 42 days before the first treatment. Treatments are then performed twice daily from V1 to V20 on work days, excluding week-ends and holidays. Subsequently, trial participants are seen at three follow-up visits, V21, V22, and V23, at 45, 90, and 180 days after baseline, respectively. The detailed trial plan is shown in Table 2.

**Table 2 T2:** Trial visits schedule.

**Action visit**	**V0 screening**	**V1 BL**	**V2**	**V3**	**V4**	**V5**	**V6**	**V7**	**V8**	**V9**	**V10**	**V11**	**V12**	**V13**	**V14**	**V15**	**V16**	**V17**	**V18**	**V19**	**V20**	**V21**	**V22**	**V23**
Day (d)		1	2	3	4	5	8	9	10	11	12	15	16	17	18	19	22	23	24	25	26	45	90	180
Permitted delta in days (±) to d1	−42		0	0	+3	+3	+4	+4	+4	+4	+4	+4	+4	+4	+4	+4	+4	+4	+4	+4	+4	±3	±4	±5
		Treatment must be completed within 30 days, with a max. of 3 consecutive non-treatment days																						
Treatment IV 2 times daily		x	x	x	x	x	x	x	x	x	x	x	x	x	x	x	x	x	x	x	x			
Screening assessment																								
Patient information, informed consent	X																							
Inclusion/exclusion criteria	X																							
Demographics	X																							
Medical history	X																							
Diagnosis according to revised EEC	X																							
Physical examination	X																							
Randomization^#^	X^#^																							
Recurrent additional status data																								
Concomitant treatment history	X	X		X				X						X							X	X	X	X
Vital signs (pulse, BP)^**^	X	X	X	X	X	X	X	X	X	X	X	X	X	X	X	X	X	X	X	X	X	X	X	X
Height (only at screening), weight	X																				X		X	X
Endpoint assessment																								
ALSFRS-R		X																			X		X	X
Vital capacity (VC)^***^	X	X																			X		X	X
ALSAQ-5		X																			X		X	X
MUNIX		X^§^																			X		X	X
ECAS		X																			X		X	X
Safety assessment																								
Laboratory tests^^*^^,^^***^^	X	X		X				X						X							X	X	X	X
Pregnancy test^***^	X																							
Adverse events	X^****^	X	X	X	X	X	X	X	X	X	X	X	X	X	X	X	X	X	X	X	X	X	X	X

* *Laboratory tests: RBC, WBC, PLT, creatinine, GFR (MDRD), ALAT, ASAT, GGT, and CK, glucose*.

** *BP and pulse. On V1-V20 to be captured before and at 0, 10, 20, 30, 45, and 60 min after each administration of trial medication*.

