#### Secondary Outcomes

Secondary endpoints are the survival time and the change of ALSFRS-R, ALSAQ-5, ECAS, MUNIX (18), and SVC from baseline to visits V20, V22 and V23. Secondary safety endpoint is safety until V20.

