### Data Recording and Study Monitoring

The documentation of the study data in adherence to the Good Clinical Practice (GCP)-guidelines and the clinical trial protocol is the responsibility of the local investigator. Original data (source documents) remain in hospital medical records and information on the eCRF must be traceable and consistent with the original data. Source documents are e.g., laboratory results, ALSFRS-R measurements, vital capacity measurements, and quality of life questionnaire. Original written informed consent signed by the patient is kept by the investigator and a signed copy will be given to the patient. No information in source documents about the identity of the patients will be disclosed. All data collected in this study must be entered in an eCRF which has to be completed by the investigator or authorized trial personnel and signed by the principle investigator. This also applies for those patients who do not complete the study. If a patient withdraws from the study, the reason must be recorded in the eCRF. The investigator is responsible for ensuring the accuracy, completeness, and timeliness of all data reported to the sponsor in the eCRFs and in all required reports.

After database lock, the principal investigator will receive data on an electronic device that includes the investigational site data for archiving in the Investigator Site File (ISF). Data are processed by data management of the CRO with the support of a study database (eCRF) according to the SOPs of the CRO. The evaluation of the data takes place by programmed validity and consistency checks.

Monitoring activities are performed to ensure that the trial is conducted in accordance with the trial protocol, the principles of GCP, and local legislation. A monitoring manual describing in detail the scope of the monitoring activities will be prepared. A monitoring visit report is prepared for each visit describing the progress of the clinical trial and all identified problems.

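### The SVC model adjusts only for the V1 baseline and leaves out the screening (V0) vital capacity: a small missed gain in precision on one secondary endpoint

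*Protocol article*

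**What the plan says.** All places are in the protocol article.

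- **Schedule (Study Procedures, Table 2).** The row beginning "Vital capacity (VC" is marked at V0, V1, V20, V22 and V23. V1 is day 1 and carries the label BL. ALSFRS-R, ALSAQ-5, MUNIX and ECAS have no mark at V0, so vital capacity is the only efficacy measure scheduled at two separate visits before treatment.
- **Gap between the two readings.** "V0 is the screening visit and may take place up to 42 days before the first treatment".
- **Stated use of the screening value (Table 1).** It serves the inclusion criterion "Vital capacity more than 65% of normal (SVC; best of three measurements".
- **Endpoint (Secondary Outcomes).** Change in "SVC from baseline to visits V20, V22 and V23".
- **Model (Secondary Analysis, Efficacy).** One MMRM serves ALSFRS-R, ALSAQ-5, SVC and MUNIX. Its terms are "treatment group, time (visits V20, V22, V23), treatment-by-time interaction", then region and onset stratum, and "baseline measurements of the outcome as covariate", with unstructured covariance. V0 is neither a response nor a covariate.
- **Data (Data Recording and Study Monitoring).** "All data collected in this study must be entered in an eCRF", so the V0 reading should be available to the analyst.

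**The concern.** Vital capacity depends on effort and is read with error. A single baseline reading therefore adjusts imperfectly for a patient's true starting level. A second reading before treatment can help in two ways: it averages out part of the test error, and the V0-to-V1 difference says something about how fast the patient was already declining.

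The V0 reading is needed to confirm eligibility, and the footnote to Table 2 allows randomisation only once the criteria have been verified. V0 thus precedes randomisation, and adjusting for it cannot bias the comparison.

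Only the width of the SVC confidence intervals is at stake. That has some interest because the Discussion (Choice of Trial Type and Design) presents efficacy as an estimate of magnitude and concedes that the trial may be underpowered for it.

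**Working it through.** **The plan's own figures.** None is given for SVC. The sample size rests on proportions and reproduces: 1.96·√(2·0.5·0.5/34) = 0.238 (stated 0.24), 1.96·√(2·0.9·0.1/34) = 0.143 (stated 0.14), and 102/0.85 = 120. SVC plays no part in it, so nothing below changes N.

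**Inputs from Table 2.** V20, V22 and V23 are on days 26, 90 and 180. At 30.4 days per month they fall T = 25/30.4 = 0.82, 89/30.4 = 2.93 and 179/30.4 = 5.89 months after V1. The longest V0-V1 gap is 42/30.4 = 1.4 months.

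**Assumed inputs (not in the documents).** Between-patient SD σ_b = 15 points; test error SD σ_e = 3, 5, 7; slope SD σ_s = 1.5, 2, 2.5 points per month; gap g = 0.25, 0.5, 1.0, 1.4 months. This gives 36 combinations. Errors at V0 and V1 are taken as independent and of equal size.

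**Model.** V1 = x + e₁; V0 = x − g·s + e₀; Y = x + T·s + e. Then:

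- Var(Y | V1) = σ_b² + T²σ_s² + σ_e² − σ_b⁴/(σ_b² + σ_e²)
- Var(V0 | V1) = σ_b² + g²σ_s² + σ_e² − σ_b⁴/(σ_b² + σ_e²)
- Cov(Y, V0 | V1) = σ_b²σ_e²/(σ_b² + σ_e²) − g·T·σ_s²
- Variance removed by adding V0 = Cov(Y, V0 | V1)² / Var(V0 | V1)

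**One case in full** (σ_e = 5, σ_s = 2, g = 0.7). Here σ_b⁴/(σ_b² + σ_e²) = 225²/250 = 202.5, and Var(V0 | V1) = 225 + 1.96 + 25 − 202.5 = 49.46.

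- V20: Cov = 22.5 − 0.7·0.82·4 = 20.20; removed 20.20²/49.46 = 8.25 of 50.19, or 16.4%; interval narrower by 1 − √0.836 = 8.6%.
- V22: Cov = 22.5 − 0.7·2.93·4 = 14.30; removed 4.13 of 81.84, or 5.0%; interval 2.6% narrower.
- V23: Cov = 22.5 − 0.7·5.89·4 = 6.01; removed 0.73 of 186.27, or 0.4%; interval 0.2% narrower.

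The covariance formula explains the pattern. Averaging out error pulls the V0 coefficient up and slope information pulls it down, more so at later visits. Where the two cancel, V0 adds nothing; where slope dominates, the gain returns with the opposite sign.

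**Over the 36 combinations:**

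| Visit | Residual variance removed: min / median / max | Interval narrower: median (max) |
|---|---|---|
| V20 | 0.3 / 15.8 / 20.8% | 8.2% (11%) |
| V22 | 0.0 / 5.3 / 15.3% | 2.7% (8%) |
| V23 | 0.0 / 1.7 / 26.2% | 0.9% (14%) |

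Changing the spacing of the grid moves the medians by well under one percentage point.

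**Check with other correlation structures (also assumed).** If all visits are equally correlated at r, the residual variance ratio is (1 + 2r)/(1 + r)²: 0.889 at r = 0.5, 0.830 at 0.7 and 0.776 at 0.9. That is an interval about 6-12% narrower. If correlation decays so that V0 informs Y only through V1 (for example 0.9 × 0.8 = 0.72), the gain is exactly zero. A steeper case outside the grid (slope SD 3, error SD 3, gap 42 days) removes 36% at V23.

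**Price of the extra term.** One more coefficient per visit costs about 94/93 − 1 = 1% of variance with 102 evaluable patients. This offsets much of the median gain at V23, and in settings where V0 adds nothing it leaves a slight net loss.

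**The case against.** The strongest reply is that nothing here is wrong. An MMRM adjusted for one baseline value and the stratification factors is conventional, valid and unbiased. The article gives one shared model sentence for four outcomes, and a second covariate for one of them is the kind of detail an analysis plan may add. All of this stands. It makes the point a suggestion about a stated choice, not a defect, and the article cannot show that the full analysis plan leaves V0 out.

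The size is also open to attack, rightly:

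- Every variance is assumed, and a median over a chosen grid is not an expected value.
- The steadiest gain is at V20, the last treatment day, when a slower decline has had least time to separate the arms. At V23, the longest follow-up, the gain is usually negligible.
- Equal quality of the two readings is not documented. A footnote to Table 2 suggests that the V0 value may be a routine clinic test.
- Selecting on V0 above 65% trims its information. With error SD 7 and an assumed mean of 80, the V20 reduction falls from 16% to about 14%.

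One reply does not hold: that the plural in "baseline measurements of the outcome as covariate" already brings in V0. The plural covers several outcomes, and only V1 is labelled baseline.

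A reader might go further and infer that the SVC analysis is biased, that the V0 value is never used, or that a substantial gain is on offer for free. The documents support none of these. Single-baseline adjustment is unbiased, V0 serves eligibility, the gain reaches zero in plausible settings, and the extra terms have a cost.

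**Conclusion.** The point holds as a modest missed efficiency. The article schedules vital capacity at V0 and V1 and then fixes an SVC model that uses only the baseline value. Under the assumed variability, adding V0 would narrow the SVC confidence interval by a median of about 8% at V20, 2-3% at V22 and 1% at V23. The floor is near zero at every visit, and larger gains at V23 appear only when slopes vary widely and the V0-V1 gap is long. The V20 figure depends on independent test errors of similar size at the two visits.

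The primary safety and tolerability analyses, the sample size of 120 and the type I error are untouched. The Discussion says that a lack of significant efficacy would not by itself argue against a follow-up study, so no decision turns on this. It is worth adopting because it is cheap, and the time to do so is before unblinding, since a covariate added later would look chosen from the data.

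**What to change.** For SVC only, in the analysis plan:

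1. Keep V1 as the reference for change from baseline and as a covariate.
2. Add the V0 vital capacity as a further covariate, crossed with visit. The visit-specific coefficient matters because the useful weight on V0 changes with time and can change sign, so a plain average of V0 and V1 would not do the same job.
3. State a rule for a missing V0 value that keeps every patient in the model, such as replacement by a value predicted from V1 in all arms pooled. Such cases should be rare, since eligibility depends on the test.

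No new data are needed. The V0 terms use up to three degrees of freedom. The calculation above also lets the V1 coefficient vary by visit, so if the baseline term is not already crossed with visit, doing so adds two more. The SVC model will differ slightly from those for ALSFRS-R, ALSAQ-5 and MUNIX, which have no V0 reading; one sentence should say why. If the analysis plan already includes V0, nothing needs to change.
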